## Methods

### Trial design

This is a randomized, parallel, placebo-controlled, double-blind, exploratory, 1:1 randomized clinical trial in one of two study groups, namely: RIC or placebo.

The study protocol follows the SPIRIT 2013 checklist (Standard Protocol Items: Recommendations for International Trials) [31] (Supplementary File 1) and the TIDieR (Template for Intervention Description and Replication) [32], so that the information and quality of reports of interventions are well described [32].

### Eligibility criteria

Women with knee osteoarthritis aged between 50 and 80 years will be included in the study if they have unilateral or bilateral knee osteoarthritis [33–35] diagnosed according to American College of Rheumatology criteria [36] which are: criteria for clinical and radiographic diagnosis (having knee pain, osteophytes and having at least one of the three items—age greater than 50 years; stiffness lasting less than 30 min and/or crepitus) or criteria for clinical diagnosis (pain in the knee and having at least three of the six items — age greater than 50 years; stiffness lasting less than 30 min; crepitus; bone enlargement; bone tenderness; no palpable heat) will be considered eligible if they are in the postmenopausal period and not present systemic rheumatic diseases (fibromyalgia, rheumatoid arthritis and systemic lupus erythematosus); congestive heart failure, peripheral vascular disease, systolic blood pressure greater than 160 or less than 100 mmHg or diastolic blood pressure greater than 100 mmHg, deep vein thrombosis, a history of acute myocardial infarction and stroke; diabetes mellitus; respiratory disease; a history of knee surgery; will not be included, as well as participants who have high levels of physical activity assessed by the Habitual Physical Activity Questionnaire [37, 38], are alcoholics, smokers, use drugs that influence cardiac autonomic modulation (beta-blockers) and have one or more predisposing risk factors for thromboembolism [39].

Participants who, in the 24 h before the test, used anti-inflammatory drugs or analgesics, performed physical activity, consumed alcohol, performed therapeutic treatments for pain relief, had errors in capturing the heart rate beat by beat (RR intervals), and wished to withdraw from the study will be excluded. In addition, participants may choose to stop performing the intervention for any reason. The flowchart of the study design and the composition of the groups is illustrated in Fig. 1.

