### Randomization and blinding

Participants who provide written informed consent will be randomly allocated to either placebo RIC or RIC. The randomization sequence will be elaborated using software (Microsoft Office Excel 2007) and will be placed in sequential numbering in opaque and sealed envelopes. A researcher who will not have contact with the participants and evaluators will generate the allocation sequence (assign the participants to the interventions). Evaluators, participants, and data analysts will be blinded to the allocation of groups. At the end of the survey, to disseminate the results to the participants, the allocation group may be revealed.

There is a study trial management group made up of the study researchers that meets weekly to monitor the progress of the study. Any changes to the protocol will be notified to the ethics committee, an update will be made to the clinical trial registry and will be communicated to study participants.

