### Study design

Data collection will be carried out at Sports Physiotherapy Laboratory at São Paulo State University (Unesp), School of Technology and Sciences, Presidente Prudente, São Paulo, Brazil. All procedures will be performed under standardized conditions (temperature: 21–23°C; relative humidity: 40–60%).

Each participant will attend the laboratory on two days separated by one week. On the first day they will be evaluated for anthropometric characteristics, using a scale (Tanita BC 554, Iron Man/Inner, Arlington Heights Illinois, USA) and a stadiometer (Sany—American Medical do Brasil, São Paulo, Brazil) and, later, the body mass index (BMI) will be calculated. Blood pressure measurements will also be performed [41] and the Knee Injury and Osteoarthritis Outcome Score (KOOS) questionnaire [42] will be applied. After these initial procedures, a 10 min rest will be performed and, in the sequence, the evaluation of total occlusion pressure (TOP) will be performed. After that, the initial CPM test will be performed, followed by the RIC, and finally the CPM test again. RR intervals will be captured from the initial 10 min of rest to the end of the complete CPM protocol.

On the second day, only the RR intervals will be captured before the RIC (15 min at rest), during, and after (15min at the end) the RIC. The study design is outlined in Fig. 2.

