#### Cardiac autonomic modulation

The collection of data will be carried out individually and the participants will be instructed to remain silent, awake, at rest, and in the supine position. The movement of people on site will be restricted, in order to reduce interference during collection. Participants will be instructed not to consume ANS stimulant substances such as alcoholic beverages, coffee, tea, soft drinks, and chocolate drinks during the 24 h prior to capturing the RR intervals.

The assessment of cardiac autonomic modulation will be performed through HRV by capturing the RR intervals using the heart rate monitor (Polar Electro Oy, Kempele, Finland – model V800) which is a validated equipment [57].

Indices obtained through linear methods, in the time domain (Mean RR, SDNN, and rMSSD), frequency (LF and HF), and the Poincaré plot (SD1 and SD2) will be analyzed [58, 59]. In addition, RR intervals will be analyzed to obtain the 30s rMSSD that represents vagal reentry. All HRV indices will be obtained using the software Kubios HRV – version 3.2 (The Biomedical Signal Analysis Group, Department of Applied Physics, University of Kuopio, Finland) [60].

For this analysis, the time series of RR intervals will be initially submitted to a digital filtering moderated by the software Kubios HRV – version 3.2 [60] complemented by manual filtering, to eliminate premature ectopic beats and artifacts, and only series with more than 95% of sinus beats will be included in the study [58]. Through the visual analysis of the time series, the absence of artifacts or ectopic beats that may interfere with the HRV analysis will be observed.

The series of RR intervals will be analyzed in two different moments: (i) during the performance of the CPM tests and (ii) during the evaluation of the RIC. In order to obtain these analyses, on the first day of the intervention, the following moments will be analyzed: M1 (10 min basal at rest before TOP), M2 (test stimuli through the algometer), M3 (conditioning stimulus, through the CPT), M4 (test stimuli through the algometer), M5 (during RIC), M6 (test stimuli through the algometer), M7 (conditioning stimulus, through the CPT), M8 (test stimuli through the algometer). In these stretches, 256 consecutive RR intervals [59] will be obtained. It is worth noting that at moments M3 and M7, only vagal reentry with a rMSSD of 30 s will be analyzed due to the short time to capture the RR intervals.

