### Statistical analysis

Statistical analysis will be conducted using SPSS software (version 18; SPSS Inc. Chicago, IL, USA). Data normality will be verified by the Kolmogorov–Smirnov test, if normality is detected, the sample characterization variables will be presented as mean and standard deviation/ if not, in median and interquartile range. To compare the characterization of the sample, Student’s *t* test will be used for independent samples.

Descriptive data of outcomes will be presented in mean, standard deviation, and confidence interval values. Comparisons of outcomes between the groups studied and the moments will be performed using Generalized Linear Mixed Models adjusted to the data with Bonferroni post-test when the main analyzes are significant. In addition, the effects of the groups studied will be verified for all outcomes evaluated by calculating the effect size (ES) through Cohen’s *d*, which will be considered as “null” (< 0.2), “small” (≥ 0.2), “moderate” (≥ 0.6), “large” (≥ 1.2) or “very large” (≥ 2.0) [67]. Intention to treat will be used and, for data imputation, a mixed linear model will be used.

To correlate CPM and cardiac autonomic modulation, the Pearson or Spearman correlation test will be used according to the normality of the data. According to the parameters of Portney and Watkins [68], the correlation magnitude of 0.00 to 0.19 is considered to be very weak; 0.20 to 0.39 weak correlation; 0.40 to 0.69 moderate correlation; 0.70 to 0.89 strong correlation and 0.90 to 1.00 very strong correlation [68]. All analyses will assume a significance level of *p* < 0.05.

The external evaluator will enter the data into the database for screening, randomization, and statistical analysis. Dual data entry in electronic format will be used. Data integrity will be monitored regularly by examining data files for omissions and errors. Participants will receive an anonymous study ID to protect confidentiality, and only study investigators will have access to the final study dataset. The spreadsheets containing the raw numerical data of the data generated in this study will be stored in their entirety initially on two external hard drives and two online clouds. Any data needed to support the protocol can be provided upon request.

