### Strengths and weaknesses of the study

In addition to not finding any studies in the literature that show a new perspective for the interaction between pain processing and cardiovascular systems in women with knee osteoarthritis, this study has other strengths, which are the high methodological quality of the study. by prospective registration, randomization, restriction of patients and evaluators, intention-to-treat approach, and comparison between a protocol of real ischemic conditioning with a placebo group, allowing to observe the result found in the intervention. We consider it as a weakness or non-blinding of the therapist.

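### Excluding participants for RR-recording errors or withdrawal, with no limit to the time before randomisation, conflicts with the stated intention-to-treat analysis

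*Protocol article*

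**What the plan says.** All references are to the protocol article.

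- **Eligibility criteria.** After the entry criteria, a second list names participants who will be excluded. It covers those who, "in the 24 h before the test, used anti-inflammatory drugs or analgesics, performed physical activity, consumed alcohol, performed therapeutic treatments for pain relief". It continues with those who "had errors in capturing the heart rate beat by beat (RR intervals), and wished to withdraw from the study will be excluded". Nothing confines the list to the time before randomisation, or says that an excluded participant stays in the analysis.
- **Cardiac autonomic modulation.** RR quality is also handled recording by recording: "only series with more than 95% of sinus beats will be included in the study".
- **Statistical analysis.** "Intention to treat will be used and, for data imputation, a mixed linear model will be used". The comparison model is named as a generalized linear mixed model.
- **Strengths and weaknesses of the study.** The listed strengths include "intention-to-treat approach, and comparison between a protocol of real ischemic conditioning with a placebo group".
- **Randomization and blinding.** "Participants who provide written informed consent will be randomly allocated to either placebo RIC or RIC". When the envelope is opened relative to the day-1 checks is not stated.
- **Study design.** "Each participant will attend the laboratory on two days separated by one week". On day 1 RR recording runs from the initial rest, through the intervention, to the end of the second CPM test. On day 2 only RR intervals are collected, before, during and after the intervention.

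**The concern.** Intention to treat with a missing-data method exists to deal with withdrawals and failed recordings. The eligibility section removes those same participants. An analyst who follows it would drop randomised participants after treatment has begun. An analyst who follows the statistical section would keep them.

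The exclusions may not be neutral between arms. One arm receives four 5-minute periods of total occlusion at the thigh; the other has a cuff at 10 mmHg. The section on adverse events acknowledges cuff discomfort and stops the procedure for pain or other symptoms. Withdrawal, and possibly movement artefact in the RR signal, could therefore differ by arm and relate to the pain response under study.

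CPM and HRV are both primary outcomes. If an RR fault excludes the participant and not just the recording, a complete CPM result is lost for a reason that has nothing to do with its quality. With 22 per arm, each such loss is 1/22 = 4.5% of an arm.

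**Working it through.** **1. When can each exclusion arise?**

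| Reason | Can it follow allocation? | Can treatment influence it? | Outcome affected |
|---|---|---|---|
| RR-capture error | Yes; recording spans and follows the intervention on both days | Plausibly, since the arms differ in exposure | HRV; also CPM if the participant is removed |
| Withdrawal | Yes | Plausibly | Both |
| 24-h breach before day 1 | Only if the envelope is already open; not stated | No; it precedes treatment | Both, if excluded |
| 24-h breach before day 2, if the rule applies there | Yes | Possibly; the window follows the day-1 intervention | HRV; CPM only if the whole participant is removed |

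The first two rows carry the point. They rest on the text alone.

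**2. The plan's sample size.** Inputs from the Sample size section: difference 98 kPa, SD 103 kPa, two-sided 5%, power 80%. The standardised effect is 98/103 = 0.951. The two-sample t-test calculation gives 18.35, so 19 per group, as stated. The loss allowance is 19 × 1.15 = 21.85, so 22 per group, as stated (19/0.85 = 22.35 would give 23). Power is 86.9% with 22 per group and 81.4% with 19. Losing the three spare participants per group therefore costs some power but keeps it above 80%. The concern is bias.

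**3. Possible bias (assumed scenario).** The documents give no exclusion rates. Simulation, 40,000 runs: no true effect, 22 per arm, outcome in SD units. The 3 RIC participants with the lowest values of a score correlated ρ with outcome are excluded, none are excluded from placebo, and 19 against 22 are compared by t test. Share removed: 3/22 = 13.6% of one arm.

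| ρ | Spurious difference (SD) | × 103 kPa | Type I error |
|---|---|---|---|
| 0 | 0.00 | 0 | 5.1% |
| 0.3 | 0.07 | about 7 kPa | 5.5% |
| 0.5 | 0.12 | about 12 kPa | 6.8% |
| 1.0 (extreme) | 0.24 | about 25 kPa | 14.1% |

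The planning difference is 98 kPa. The sign of the bias depends on which participants are lost.

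**4. Imputation (conditional).** Simulation, 20,000 runs: 22 per arm, baseline-outcome correlation 0.5, 3 missing per arm. Each missing value is replaced by its fitted value from group and baseline, and the completed data are analysed by ANCOVA as if fully observed. Type I error is 9.1%; two repeat runs gave 8.7% and 9.5%. Across 3 to 5 missing per arm, the same model on observed data only gave 4.8% to 5.1%. Three missing per arm matches the plan's loss allowance.

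**The case against.** - **Exclusion could mean stopping participation, with the gaps then handled under intention to treat.** The series-level rule in the HRV section leans that way. This stands as an ambiguity: the two rules are not strictly impossible to reconcile. But the eligibility sentence is about participants, and nothing says they remain in the analysis.
- **A reader might infer that allocation happens at consent, so every 24-h breach is a post-randomisation exclusion that treatment can influence.** The documents do not support this. They say who is randomised, not when the envelope is opened, and the flowchart is not shown. A day-1 breach precedes treatment in any case.
- **The 24-h rule may not reach day 2.** It refers to a single test, and day 2 has no CPM test. This stands: the day-2 route is conditional and bears on HRV unless the whole participant is removed.
- **A reader might infer that the imputation as written inflates type I error.** It does not follow. The sentence does not say whether imputation is single or multiple, or whether it precedes the comparison model. It may loosely describe likelihood-based handling within the mixed model. That detail may properly sit in an analysis plan that is not shown.
- **The bias is assumed, modest at moderate correlations, and the trial is labelled exploratory.** This stands and limits the size of the claim. It does not remove the conflict between sections.

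**Conclusion.** The conflict is real for RR-capture errors and withdrawals. A stated rule would remove randomised participants for reasons that treatment can influence, in a trial that claims intention to treat as a strength. Read at participant level, it would also discard usable CPM data.

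The size of any bias cannot be derived from the documents. Under one-arm exclusion of 3 of 22, it is nil if exclusion is unrelated to outcome. It is about 0.07 to 0.12 SD, with type I error of about 5.5% to 7%, at correlations of 0.3 to 0.5. The 14% figure needs a correlation of 1 and should not be taken as expected. Whether artefact or withdrawal will in fact differ by arm is plausible but not shown. The type I error of about 9% from imputation applies only if single filled-in values are treated as observed.

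**What to change.** 1. State that all randomised participants are analysed in the group to which they were allocated.
2. State that an unusable RR series sets only that HRV segment to missing. The participant stays in the CPM analysis and in the other HRV analyses.
3. Keep all data collected before withdrawal. Report withdrawals and unusable recordings by arm.
4. Open the envelope only after the day-1 24-h, blood pressure and baseline CPM checks are complete.
5. Say whether the 24-h rule applies to day 2, reconcile it with intention to treat, and report breaches by arm. How a breach affects the visit schedule is for the investigators to settle.
6. Fit the mixed model to all observed data without a separate imputation step. If imputation is kept, use a method that carries its uncertainty and does not treat single filled-in values as observed.

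The cost is changed wording and a later envelope opening. No extra participants are needed.

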**Fig. 1 Fig1:**
[figure not shown]
Flowchart of the study design. RIC, remote ischemic conditioning; P-RIC, placebo remote ischemic conditioning

### Recruitment

Participants will be recruited through advertising folders on the institution’s premises, health centers, and social networks. These procedures are recommended by Treweek et al. [40] as strategies to improve the recruitment of participants.

All participants will undergo an initial telephone screening to determine eligibility for inclusion in the study. The following data will be obtained as part of the screening: age, self-reported weight, brief health history including symptoms of knee osteoarthritis (knee joint pain and stiffness), patient comorbidities, and medications in use. Afterwards, the participants will answer the Habitual Physical Activity Questionnaire [38, 39] that assesses the level of physical activity. Those who claim to have knee pain and meet the study inclusion criteria will be invited to remain in the study. The blood pressure eligibility criteria will be personally measured to confirm the pressure measurement reported by the participant over the phone.

Initial assessment data will also be used for sample characterization purposes. If eligible and willing to participate in the study, a time will be scheduled for the participant to attend the Sports Physiotherapy Laboratory. To increase the participants’ adherence to the intervention, telephone contact will be made daily to encourage them to remain in the study, and thus avoid losses.

All participants will go through an informed consent process that will include the delivery of written information about the need and the overall benefit of the study, followed by a discussion with a researcher. This discussion will include verifying their understanding of the benefits and risks of participation and ensuring that participants accept that treatment will be randomly allocated, regardless of any personal preferences they may have. If the participant agrees to participate, a consent form is signed (the consent form template is in the  supplementary materials).

The consent form does not ask whether participants would like to be contacted in the future about research participation. It is worth noting that this study will not perform laboratory evaluation and storage of biological specimens for genetic or molecular analysis at this time or for future use.

### Randomization and blinding

Participants who provide written informed consent will be randomly allocated to either placebo RIC or RIC. The randomization sequence will be elaborated using software (Microsoft Office Excel 2007) and will be placed in sequential numbering in opaque and sealed envelopes. A researcher who will not have contact with the participants and evaluators will generate the allocation sequence (assign the participants to the interventions). Evaluators, participants, and data analysts will be blinded to the allocation of groups. At the end of the survey, to disseminate the results to the participants, the allocation group may be revealed.

There is a study trial management group made up of the study researchers that meets weekly to monitor the progress of the study. Any changes to the protocol will be notified to the ethics committee, an update will be made to the clinical trial registry and will be communicated to study participants.

### Study design

Data collection will be carried out at Sports Physiotherapy Laboratory at São Paulo State University (Unesp), School of Technology and Sciences, Presidente Prudente, São Paulo, Brazil. All procedures will be performed under standardized conditions (temperature: 21–23°C; relative humidity: 40–60%).

Each participant will attend the laboratory on two days separated by one week. On the first day they will be evaluated for anthropometric characteristics, using a scale (Tanita BC 554, Iron Man/Inner, Arlington Heights Illinois, USA) and a stadiometer (Sany—American Medical do Brasil, São Paulo, Brazil) and, later, the body mass index (BMI) will be calculated. Blood pressure measurements will also be performed [41] and the Knee Injury and Osteoarthritis Outcome Score (KOOS) questionnaire [42] will be applied. After these initial procedures, a 10 min rest will be performed and, in the sequence, the evaluation of total occlusion pressure (TOP) will be performed. After that, the initial CPM test will be performed, followed by the RIC, and finally the CPM test again. RR intervals will be captured from the initial 10 min of rest to the end of the complete CPM protocol.

On the second day, only the RR intervals will be captured before the RIC (15 min at rest), during, and after (15min at the end) the RIC. The study design is outlined in Fig. 2.

**Fig. 2 Fig2:**
[figure not shown]
Study design. BMI, body mass index; BP, blood pressure; RR-I, RR intervals; M, moment; TOP, total occlusion pressure; CPM1, initial conditioned pain modulation; CPM2, final conditioned pain modulation; RIC, remote ischemic conditioning; P-RIC, placebo remote ischemic conditioning

